#### **Signing of informed consent.**

Patients of the present trial signed an informed consent to participate at the study up to 18 months. This trial was prolonged to 24 months. We will propose another informed consent to patients for the prolongation of the study. The objectives of this prolongation will be explained to all the patients and they will sign the third informed consent. They will be examined for the two last calibrated blood smears as at M14 and M18.

#### **Subject Compensation**

Subjects who accept to continue the study and who signs the informed consent will be compensated for any expenses incurred during the transport to the study site but will not have direct financial compensation for study participation.

#### **Information of the subjects of the study results**

During explanation for the continuation of the study, the investigators will explain the tendency of the LLM of each patient. This explanation will be completed when the final data from the study will be available. Each patient will be informed individually about the evolution of his *Loa loa* microfilaremia.

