#### **6.1.3.6 Subject information on screening results**

Subjects will be informed individually verbally of the results of the examinations performed on them and also provided cards with their name (and photo unless they do not want one) and the results of all tests performed as well as all treatments administered based on the results of the examinations performed during the screening.

For subjects who participate in the study, these cards will be updated with any results relevant to their medical history that may be obtained during the examinations performed during the course of the study.

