### 9.2 Statistical Methods

#### 9.2.1 Efficacy analysis

Proportions of patients with a sustained reduction of LLM from baseline by  $\geq 50\%$  between each active treatment group and the placebo group will be compared by the Chi square test.

*Loa* parasitaemia will be compared at each point between groups using non-parametric test due to the non normal distribution of the *Loa* microfilaraemia. The General Linear Model (GLM) will also be used for the comparison of the evolution of *Loa* parasitemia in different groups.

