### 9.2.3 Analysis populations

Two populations will be analyzed for efficacy:

Per protocol population: includes all subjects who were received the full treatment course they were randomized to and have a final efficacy assessment. .

Intent to treat population: includes all subjects who received at least one dose of study drug and have a final efficacy assessment.

All subjects who received at least one dose of study drug will be included in the safety analysis.

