## **Protocol Amendment**

### **Efficacy of albendazole in decreasing *Loa loa* microfilaraemia**

The protocol of the study on the Efficacy of albendazole in decreasing *Loa loa* microfilaraemia started in March 2007 in the south Province of Cameroon. This study which was a double blind study had to continue until 18 month (September 2008). The study continued to this term and the blind was lifted. Due to tendency of decrease in one of the group, it was proposed that the follow-up should continue to 24 months with two supplementary control of the *Loa loa* microfilaremia at M21 and M24.

The procedure of blood sampling will remain as from M0 to M24. The blood sample will be collected almost and the same time, with the same material and with the same precautions. The examination of slides will follow the same procedures as the previous examinations.

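### Subjects hear their own microfilaraemia trend while being asked to consent to M21 and M24, so attendance there may depend on the outcome, and a comparison of attendees could be biased in either direction

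*Protocol*

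**What the plan says.** The amendment records that the study ran to month 18: "The study continued to this term and the blind was lifted". It then gives the reason for going on: "Due to tendency of decrease in one of the group, it was proposed that the follow-up should continue to 24 months", with added smears at M21 and M24.

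The existing consent covered 18 months only, so under Signing of informed consent the amendment states: "We will propose another informed consent to patients for the prolongation of the study". Subject Compensation refers to those who agree: "Subjects who accept to continue the study and who signs the informed consent will be compensated". Information of the subjects of the study results fixes what they are told in that conversation: "During explanation for the continuation of the study, the investigators will explain the tendency of the LLM of each patient". A fuller explanation follows once the final data are available.

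The amendment states no analysis for M21 or M24. The protocol's section 9.2.1 says that "parasitaemia will be compared at each point between groups using non-parametric test", and adds a General Linear Model for the evolution over time. Under section 9.2.3 the intent-to-treat population "includes all subjects who received at least one dose of study drug and have a final efficacy assessment". The per-protocol population carries the same requirement. Neither document part says whether the final assessment is still M18 or is now M24.

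**The concern.** Each subject learns his or her own result in the conversation that decides who supplies the next result. Someone told of a fall and someone told of none may have different reasons to go on. If so, M21 and M24 are observed in a sample chosen partly on the outcome.

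The extension exists to see whether the fall in one arm persists. A change in who attends can imitate a continuing fall, or hide one, without any subject's count changing. Calling the extra visits exploratory does not remove this. It is a separate matter from the extension having been prompted by unblinded data.

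There is also a way into the main efficacy populations. If the final efficacy assessment is read as M24, a subject who declines the extension drops out of both of them despite complete data to M18.

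**Working it through.** **Inputs.** The protocol gives no continuation rate, no standard deviation for within-subject change and no figure for M21 or M24, so there is no stated result to reproduce. The nearest planning figures are in section 9.1: 16 per arm and about 20% dropout, 16/(1 − 0.20) = 20, which reproduces the stated 20 but covers the 18-month study only; and an assumed response of at least 50% on albendazole against almost none on placebo. All continuation rates and spreads below are assumptions.

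**Step 1: one arm with mixed responses.** Let half the arm sit at 25% of baseline and half at 100%. The geometric mean at M18 is 0.25^0.5 = 0.500. No count changes afterwards. If fallers continue with probability p and the others with probability q, the faller share among attendees is s = 0.5p/(0.5p + 0.5q) and their geometric mean is 0.25^s.

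- p = 0.90, q = 0.60: s = 0.45/0.75 = 0.60; 0.25^0.60 = 0.435. Since 0.435/0.500 = 0.87, this is an apparent further fall of 13%.
- p = 0.95, q = 0.50: s = 0.475/0.725 = 0.655; 0.25^0.655 = 0.403. An apparent fall of 19%.
- p = 0.60, q = 0.90: s = 0.30/0.75 = 0.40; 0.25^0.40 = 0.574. Since 0.574/0.500 = 1.15, this is an apparent rise of 15%.
- p = q: s = 0.50; 0.500. No bias.

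**Step 2: one arm with no true change.** Here log(LLM/baseline) is normal with mean 0 and SD 0.3 to 0.8, with correlation 0.7 or 1.0 between the disclosed trend and M24. If subjects told of a fall continue more often (90/70% up to 100/50%), simulated attendees show 81% to 98% of baseline. If they continue less often (70/90% or 60/95%), attendees show 102% to 116%. At 80% in both groups they show 100%.

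**Step 3: between arms, which is what section 9.2.1 tests.**

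- Arms that differ by a uniform shift, same consent rule in both: a true ratio of 0.60 becomes 0.61 to 0.63 when fallers stay and 0.59 to 0.60 when they leave. With no true difference and 18 per arm approached, the rank test rejects 4.8% of the time at a nominal 5%. The selection largely cancels.
- Mixed active arm as in step 1, placebo at 100%, log-SD 0.3 to 0.8 in both, same consent rule in both, true ratio 0.50: if a fall means below half of baseline, attendees show 0.41 to 0.46 when fallers stay (90/60% or 95/50%) and 0.55 to 0.57 when they leave (60/90%). If any drop below baseline counts as a fall, the fallers-stay figures are only about 0.47 to 0.50.
- Consent rules that differ by arm, no true difference: the rank test rejects 9.0% (80/80% against 100/50%) to 11.8% (95/60% against 60/95%) of the time at a nominal 5%.

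**Step 4: does conditioning on the disclosed data help?** In the mixed-arm case, regressing M24 on M18 within arm among attendees, and averaging the prediction over everyone with an M18 count, returns a ratio of about 0.50, the true value.

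**Step 5: the primary response.** It needs a reduction of at least 50% lasting at least 4 months. Smears at M2 to M10, M14 and M18 allow this to be judged, with M14 to M18 as the last possible 4-month window. All of these samples precede the disclosure.

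**The case against.** The case against is substantial, and much of it stands.

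- Dependence is possible but not shown. The amendment writes as if all patients will sign, and if nearly all do, there is nothing to correct. A reader might infer that continuation does depend on the outcome, or that the extension will show a fall that did not happen. The documents support neither: they give no continuation data, and subjects without a fall may be the keener ones to stay.
- The prescribed by-visit test is between groups, and equal selection in similarly behaving arms largely cancels. This stands for a uniform shift. It fails where responses are mixed in one arm, which resembles the protocol's own planning case, or where selection differs by arm. The lifted blind makes the latter possible, although the amendment mentions disclosing the subject's own trend, not the arm.
- M18 is not an unselected reference, because about 20% dropout is expected by then. Section 6.1.3.6 also says that "these cards will be updated with any results relevant to their medical history", so some subjects may have known their counts already.
- Section 9.2.1 also plans a General Linear Model. That is a fair reminder, but the protocol does not say whether it would keep subjects who stop at M18.
- Telling people their results when asking them for more samples is a defensible ethical choice. A reader might treat the timing as a statistical mistake to be reversed. The documents do not support that, and it is not argued here.

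**Conclusion.** The point holds in limited form. The amendment ties individual outcome disclosure to the consent for M21 and M24, so attendance there may depend on the observed outcome. A by-visit comparison of attendees, or efficacy populations that depend on an M24 assessment, could then be biased in either direction: within an arm, and between arms where one arm has mixed responses.

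Under the assumed rates, a mixed arm truly at 50% of baseline would show about 40% to 57%, and a true between-arm ratio of 0.50 would show 0.41 to 0.57. These ranges rest wholly on assumed continuation rates, spreads and definition of a fall. The bias is nil if nearly all continue or if continuation is unrelated to the trend.

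A reader might also infer that the main efficacy result is compromised. It is not, provided the final efficacy assessment remains M18 and the two later visits are kept out of the primary response.

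**What to change.** Three additions to the amendment or the analysis plan:

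1. State that the final efficacy assessment defining both efficacy populations remains M18, so that declining the extension removes nobody from them.
2. Analyse M21 and M24 as exploratory, with a likelihood-based repeated-measures model of log LLM that keeps all M0 to M18 counts of every subject, whether or not they re-consent. Selection on the disclosed, recorded trend is then conditioned on; selection on anything unrecorded is not.
3. Beside any M21 or M24 figure, report the M18 LLM of continuers and non-continuers by arm, with the number in each group.

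The cost is a few sentences and a little more analysis of data already held. No visit, sample or procedure changes. The timing of the individual disclosure is for the sponsor and the ethics committees to weigh and is not part of this fix.
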